## Abstract

**Background:**

Over 3000 young people under the age of 18 are admitted to Tier 4 Child and Adolescent Mental Health Services (CAMHS) inpatient units across the UK each year. The average length of hospital stay for young people across all psychiatric units in the UK is 120 days. Research is needed to identify the most effective and efficient ways to care for young people (YP) with psychiatric emergencies. This study aims to evaluate the clinical effectiveness and cost-effectiveness of intensive community care service (ICCS) compared to treatment as usual (TAU) for young people with psychiatric emergencies.

**Methods:**

This is a multicentre two-arm randomized controlled trial (RCT) with an internal pilot phase. Young people aged 12 to < 18 considered for admission at participating NHS organizations across the UK will be randomized 1:1 to either TAU or ICCS. The primary outcome is the time to return to or start education, employment, or training (EET) at 6 months post-randomization. Secondary outcomes will include evaluations of mental health and overall well-being and patient satisfaction. Service use and costs and cost-effectiveness will also be explored. Intention-to-treat analysis will be adopted. The trial is expected to be completed within 42 months, with an internal pilot phase in the first 12 months to assess the recruitment feasibility. A process evaluation using visual semi-structured interviews will be conducted with 42 young people and 42 healthcare workers.

**Discussion:**

This trial is the first well-powered randomized controlled trial evaluating the clinical and cost-effectiveness of ICCS compared to TAU for young people with psychiatric emergencies in Great Britain.

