#### Sample size {14}

The sample size calculation is based on Ougrin et al (2018) [23] which estimated the proportion of young people not in employment, education or training (NEET) at 6 months follow-up as 49% for the control arm (TAU) and 19% for the intervention arm, indicating a difference of 30% (95% CI from 13.1 to 47.3%). In line with the Adult IAPT targets of achieving 50% recovery versus baseline 30% recovery [27], a reduction of 20% or larger in the proportion of young people NEET is clinically significant and therefore the minimum clinically significant (proportion) difference (MCID) is set to 20% (49% NEET under TAU and 29% NEET under ICCS), which is at the lower end of the CI for the effect size. An adjustment of 5% for loss to follow-up was used based on the findings from Ougrin et al (2014) [14]. A sample size of 252 participants, with 126 participants per trial arm, is required to detect a 20% reduction in the proportion of young people NEET with 90% power using a two-sided log-rank test. The sample size for the semi-structured qualitative interviews is based on recommendations for deciding saturation in theory-based interview studies. At least 42 young people will be recruited, 21 with experience of ICCS and 21 with experience of inpatient care. In addition to the service users, we will interview 42 mental health professionals delivering both intensive community care and inpatient care to examine their experience of care and treatment delivery.

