#### Internal pilot

A 12-month pilot will assess whether enough eligible patients can be recruited in 12 months to make a trial viable within the proposed 36-month main trial recruitment period. To progress, the trial must recruit 55 patients in total. Recruiting 60–80% (41–54) of the projected recruitment will trigger a discussion with the funder to remedy recruitment difficulties. Recruiting less than 60% (< 41) will indicate that the trial should not proceed. The overall schema for the trial is shown in Fig. 1.

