## Discussion

Community-based treatment and inpatient admission are distinct models of care. The existing research is not sufficient to determine their relative effectiveness to enable evidence-informed policymaking and service planning. The IVY study is the only study to date with substantial potential to address the uncertainties in the true clinical and cost-effectiveness of ICCS as an alternative to inpatient admission. The IVY study is a definitive RCT in a real-life healthcare setting, at multiple sites with a representative geographical spread and a range of clinicians from diverse disciplinary backgrounds. We chose time to EET as the primary outcome measure because economic studies have shown that achieving both health and employment outcomes is necessary to generate better social and economic benefits for individuals and society [37]. This outcome measure is also compatible with the National Mental Health Service Dataset, making the trial results highly compelling to policymakers, healthcare providers, and mental health researchers. The trial results could lead to positive changes in clinical practice, such as developing new guidelines. The IVY study will evaluate ICCS's impact on a wide range of symptomatology and health outcomes experienced by young people with psychiatric emergencies, including self-harm, suicidality, general health, and well-being. The study will also provide accurate information about the services accessed under ICCS and TAU. A comprehensive cost-effectiveness evaluation will assess costs offset and costs saved by ICCS compared to TAU. Thus, the IVY study will provide unprecedented data on the relative clinical effectiveness, cost-effectiveness, and service utilization of ICCS and TAU for young people with psychiatric emergencies.

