### Trial status

The current protocol is version 2.7, dated August 10, 2023. The IVY study started in October 2020 and was paused from March 2020 until the end of September 2021 due to the coronavirus pandemic. COVID-19 caused a pause in a large proportion of NHS research, including the IVY study, which was also affected by the closure of UK schools, as the primary efficacy parameter of the study is time to EET. Site activation was staggered with sites reopening for recruitment 6 months after project restart, due to a backlog in internal review processes from disruptions caused by the pandemic and staff shortages. SAP for this trial was approved by the TSC chair in November 2022. Recruitment restarted in February 2022, but was stopped in September 2023 due to not meeting the progression criteria for the internal pilot. Patient follow-up is ongoing, with the final follow-up visit scheduled for February 2024.

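### The article calls the trial well-powered and definitive without qualification, although it reports that recruitment stopped because the internal pilot missed its progression criteria

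*Protocol article*

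**What the plan says.** The abstract's Discussion paragraph says "This trial is the first well-powered randomized controlled trial evaluating the clinical and cost-effectiveness of ICCS compared to TAU". The main Discussion says "The IVY study is a definitive RCT in a real-life healthcare setting". Both are in the present tense and unqualified.

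Sample size {14} sets the target: "A sample size of 252 participants, with 126 participants per trial arm, is required", for 90% power with a two-sided log-rank test at "49% NEET under TAU and 29% NEET under ICCS".

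The Internal pilot section sets the progression rule for the first 12 months: "To progress, the trial must recruit 55 patients in total". A count of 41 to 54 triggers a discussion with the funder, and fewer than 41 indicates that the trial should not proceed. Trial design {8} uses the term definitive trial only for the phase that follows a green pilot result.

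Trial status says that recruitment restarted in February 2022 and "was stopped in September 2023 due to not meeting the progression criteria for the internal pilot". Only follow-up continues, to February 2024. The article gives no number randomized and no revised power or precision.

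**The concern.** Adequate power is tied to 252 participants, and the article's own term definitive is tied to passing the pilot. The trial was stopped because it did not pass. The two descriptions therefore apply to the trial that was planned, while their wording applies them to the trial that will be analysed.

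The risk lies in interpretation. A non-significant hazard ratio from a trial that its authors call well powered and definitive invites the conclusion that intensive community care (ICCS) is no better than treatment as usual (TAU). In a much smaller trial, such a result would be compatible with the full effect the trial was designed to find. A significant result would tend to overestimate the effect. The Discussion expects the results to influence policymakers and possibly guidelines, so the description matters.

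**Working it through.** **Inputs**
- NEET at 6 months, 49% (TAU) and 29% (ICCS): Sample size {14}. The event probabilities are 51% and 71%, mean 61%.
- Loss to follow-up 5%: Sample size {14}.
- 1:1 allocation: Sequence generation {16a}.
- Two-sided alpha 0.05: assumed. The article states none, but a 95% CI is planned for the hazard ratio.
- Number randomized: not stated, so a range is shown.

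**Step 1. Reproduce the planned figure.** The article says 252 is "required to detect a 20% reduction in the proportion of young people NEET with 90% power using a two-sided log-rank test".
- HR = ln(0.29)/ln(0.49) = 1.735 under proportional hazards.
- Freedman events = (1.960 + 1.282)² × [(HR + 1)/(HR − 1)]² = 10.51 × 13.84 = 145.4, so 146.
- 146/0.61 = 239.3, so 240 patients. Then 240 × 1.05 = 252, or 240/0.95 = 252.6, so 253.

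The planned figure reproduces. At 252, expected events are 252 × 0.95 × 0.61 = 146.0, and power is 90.1% (Freedman) or 91.5% (Schoenfeld).

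**Step 2. Apply the same effect to smaller numbers.**
- Events d = N × 0.95 × 0.61.
- Freedman power = Φ(0.2688 × √d − 1.96), where 0.2688 = (HR − 1)/(HR + 1).
- Schoenfeld power = Φ(0.551 × √d/2 − 1.96), where 0.551 = ln HR.
- The 95% CI multiplies and divides the HR by exp(1.96 × 2/√d).

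| Assumed N | Why this N | Events | Power (Freedman to Schoenfeld) | CI factor |
|---|---|---|---|---|
| 30 | well inside the stop band | 17.4 | 20-21% | 2.6 |
| 40 | top of the stop band (fewer than 41) | 23.2 | 25-26% | 2.3 |
| 54 | one short of the progression count | 31.3 | 32-34% | 2.0 |
| 68 | full pilot projection, 41/0.60 = 68.3 | 39.4 | 39-41% | 1.9 |
| 87 | 55 × 19/12 = 87.1 | 50.4 | 48-50% | 1.7 |
| 252 | plan | 146.0 | 90-92% | 1.4 |

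The row for 87 assumes that the 12-month target rate was very nearly held for the 19 months from February 2022 to September 2023.

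**Step 3. Number needed for 80% power.** Here (1.960 + 0.842)² = 7.85.
- Schoenfeld: 7.85 × 4/0.551² = 103.3 events, and 103.3/(0.95 × 0.61) = 178 patients.
- Freedman: 7.85 × 13.84 = 108.6 events, and 108.6/(0.95 × 0.61) = 187 patients.

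That is more than three times the progression count of 55.

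**The case against.** The strongest reply is that a protocol article describes a plan. Version 2.7 is dated August 2023, before the stop, and the stop and its reason are disclosed in Trial status. This holds for the design sections. The planned 252 and the superiority hypothesis are not errors, and the stop is not concealed. It does not cover the two disputed sentences. The article was completed after the stop, the sentences describe the trial itself, and one closes the abstract, where many readers never reach Trial status.

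A second reply is that the true effect may be larger. At the earlier study's 49% versus 19% (HR = ln(0.19)/ln(0.49) = 2.33, mean event probability 66%), Schoenfeld power would be about 56% at 40 patients, 69% at 54 and 87% at 86. The article, however, sized the trial on the 20-point difference that it calls clinically significant, and its 90% refers to that.

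Three stronger readings are tempting, and the document does not support them:
- **That actual power is known to be about 26% to 50%.** The final number is not given, nor which band was missed. If total enrolment stayed below 55, power is at most about 34%. The 50% end needs about 87 to 92 patients, and staggered site activation makes a constant rate doubtful. Nor is 26% a floor, since fewer than 40 patients gives less.
- **That the SAP ignores the early stop.** Its approval in November 2022 preceded the stop, but the SAP is not shown and a later amendment cannot be excluded.
- **That the cost-effectiveness analysis needs the same caveat on non-significance.** It is planned with net benefit and acceptability curves, not a significance test.

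**Conclusion.** The point holds as an internal contradiction. It is not an arithmetic error: the calculation behind 252 is correct for the planned design. The unqualified claims of being well powered and definitive are incompatible with the reported stop and with the article's own use of definitive for the phase after progression.

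The size depends on an unstated number. For 40 to 87 patients, power for the planned effect is about 25% to 50%, and the CI factor is 2.3 to 1.7 instead of 1.4. No number in the range examined comes near the 178-187 needed for 80%. These figures rest on two-sided alpha 0.05, 5% loss, proportional hazards and 49% versus 29%. They do not allow for the random trust effects in the planned Cox model. The contradiction itself needs none of these assumptions.

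**What to change.** - In the abstract and the Discussion, limit well-powered and definitive to the planned design, and say there that recruitment stopped at the pilot stage.
- In Trial status, state the number randomized, the expected events, and the power and CI width these give for an HR of 1.735.
- Before database lock, confirm that the SAP states how an early-stopped trial will be interpreted, or amend it to do so: a non-significant hazard ratio is not to be read as evidence of no difference. The hazard ratio with 95% CI is already the planned estimate, so the model need not change.

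The cost is a few sentences and, if needed, a short SAP amendment. The downside is that the stated power becomes much less favourable.

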**Trial registration:**

ISRCTN ISRCTN42999542, Registration on April 29, 2020

## Administrative information

Note: the numbers in curly brackets in this protocol refer to SPIRIT checklist item numbers. The order of the items has been modified to group similar items (see http://www.equator-network.org/reporting-guidelines/spirit-2013-statement-defining-standard-protocol-items-for-clinical-trials/).

## Introduction

### Background and rationale {6a}

A 2022 National Health Service (NHS) survey of children and young people’s (CYP) mental health in England found that around 1 in 6 children aged 5–16 years were identified as having a probable mental health problem [1]. The latest review of CAMHS (which include specialist and inpatient services) revealed that there were over 1.2 million CYP aged between 0 and 18 years referred for mental health support in 2021–2022, an increase of 41% since 2010–2021 [2]. Inpatient admissions for CYP can play an important role in providing intensive levels of care to stabilize severe mental health disturbances [3]. However, they can also be lengthy with interpersonal disconnection [4]. This is especially true for CYP who experience repeated admissions [5]. Over 1000 CYP have been placed ‘out of area’ for mental health care in England each year for the past 3 years, most detained under the Mental Health Act [6]. From 2021 to 2022, there was a 32% increase in the number of under-18s admitted to adult psychiatric wards in England, with 260 admissions compared to 197 in the previous year. The main reason for these admissions was a lack of alternative mental health inpatient or outreach services for CYP [7]. Inpatient admissions are more costly for healthcare systems than outpatient care. Demand can also outstrip capacity, resulting in admissions of CYP in adult psychiatric wards or non-mental health inpatient settings [8].

The COVID-19 pandemic has seen a worldwide increase in psychiatric emergencies [9], exacerbating the national bed crisis in the UK. The average length of hospital stay in the UK is 74 days for general admissions, 103 days for eating disorders units, and 307 days for secure units, which is longer than in many other developed countries [10]. A key contributor to the long length of hospital stay for CYP with mental health problems in the UK is an underdeveloped network of services designed to provide alternatives to inpatient care. Safe and effective interventions that can act as alternatives to inpatient admissions for CYP presenting in crisis are therefore highly desirable. Policymakers are increasingly recognizing this need, and in the UK strategies are in place to improve community mental health services [11]. NHS England typically commissions CAMHS specialist services through a competitive tendering process and involves several different stakeholders, including local authorities, providers, and patients and their families [12].

ICCS are a type of CAMHS specialist service for CYP with severe mental health problems that provide intensive treatment primarily outside of hospital in a community setting such as schools, homes, and religious or cultural centres [13]. ICCS are multidisciplinary teams of professionals, such as psychiatrists, psychologists, social workers, and nurses, who use a mix of evidence-based interventions to provide the best possible support to each child or young person, depending on their individual needs. These interventions may include supported discharge [14, 15], home treatment [16], intensive case management [17], assertive community treatment [18], and multisystemic therapy [19]. ICCS must meet minimum operational requirements across four themes [13]: (1) organizational boundaries (comply with admission criteria, adopt integrated models of care, provide out-of-hours support, active involvement in inpatient admission, timely and safe discharge), (2) human resources (caseload ratio of ≤ 10 service user to 1 provider, direct clinician contact per week of ≥ 2 episodes for at least 90% of caseload, team meetings ≥ 1 per week, monitoring of caseloads by ICCS lead, minimum ICCS team size of ≥ 4 FTE staff, clinical supervision of ≥ 1 per month for individual staff members, access to ≥ 1 psychiatrist or psychiatric prescriber), (3) nature and scope of services (≥ 80% of face-to-face contacts in community setting, advocating service user engagement with community resources, holistic approach to service user engagement, direct clinical contact for each service user on caseload of ≥ 2 h per week), and (4) evaluation (using mental health outcome measures to review and monitor service user progress). NHS-Led Provider Collaboratives are supporting the development of ICCS across England in line with the aims and investment priorities of Five Year Forward View for Mental Health to provide an alternative to admission to Tier 4 mental health facilities. Systematic reviews from 2009 [20], 2016 [21], and 2021 [22] did not find sufficient quality data to recommend a specific type of intervention as an alternative to inpatient admission for CYP presenting in mental health crisis. ICCS remains underutilized despite the accumulating evidence that it can provide a cost-effective alternative to inpatient care with similar clinical outcomes [23, 24].

### Objectives {7}

The primary trial objective is to evaluate the clinical effectiveness of ICCS compared to the treatment as usual (TAU) in improving the time taken for YP to return to or start EET, as measured by the number of days from randomization to the first day of attending EET. Secondary objectives are to (1) determine the relative effectiveness of ICCS in improving clinical outcomes and service satisfaction, (2) assess the relative cost-effectiveness of ICCS, (3) explore the experiences of CYP who receive ICCS, including their perceptions of the benefits and challenges of the intervention, and (4) explore the experiences of mental health professionals in delivering ICCS, including their perspectives on the strengths and weaknesses of the intervention.

### Trial design {8}

This is a non-commercial, multi-centre, parallel-group, single-blind (outcome assessor) randomized controlled superiority trial to test the hypothesis that young people randomized to ICCS will return to or gain EET significantly faster than young people who receive TAU when tested at 6 months post-randomization (a follow-up). A nested qualitative semi-structured interview study will explore service user experiences of inpatient care or ICCS treatment, and service provider experiences in delivering either ICCS or TAU. The trial was designed with two phases so that potential recruitment barriers within the first phase (an internal pilot) can be resolved before the second phase (the main trial). Progression to the main trial will depend on achieving projected recruitment targets within the first 12 months of the start of the RCT and will be reviewed with the trial steering committee (TSC) and the funder, National Institute for Health Research Health Technology Assessment Programme (NIHR-HTA). The trial schema is shown in Fig. 1. A traffic light system will be used to assess whether it is warranted and feasible to progress to the second phase:Green (go): progression to definitive trial if 80–100% of projected target is achieved.Amber (amend): review/amend recruitment strategies if 60–80% of the projected target is achieved.Red (stop): the study should not process as planned if < 60% of the projected target is achieved.

**Fig. 1 Fig1:**
[figure not shown]
The trial schema shows the number of patients to recruit in Phase 1 (internal pilot) and the progression criterion to Phase 2 (main trial)

## Methods: participants, interventions and outcomes

### Study setting {9}

Participants will be recruited at nine centres participating in the trial: South London and Maudsley NHS Foundation Trust, East London NHS Foundation Trust, North East London NHS Foundation Trust, Central and North West London NHS Foundation Trust, Oxford Health NHS Foundation Trust, NHS Lothian, Berkshire Healthcare NHS Foundation Trust, Cambridgeshire and Peterborough NHS Foundation Trust, and Cwm Taf Morgannwg University Health Board. All centres will run the trial in accordance with good clinical practice guidelines and will work in collaboration with NIHR local research networks and with the King’s Clinical Trials Unit (KCTU).

### Eligibility criteria {10}

Inclusion and exclusion criteria for study participants are detailed in Table 1.

**Table 1 Tab1:** Inclusion and exclusion criteria

Inclusion	Exclusion
1. Young people aged 12 years 0 months to 17 years 11 months (exclude if 18 at randomization) 2. Young people who can consent* and who are being considered for in-patient psychiatric admission or ICCS in the participating NHS Trusts. * Eligible participants under 16 years of age will require the consent of at least one person with parental responsibility	1. Local ICCS or TAU teams unable to accept new referrals due to their full capacity being reached. 2. Young people unable to consent due to their mental state. 3. The young person’s risk profile is incompatible with ensuring their safety and/or the safety of others in the community, as indicated by a Children’s Global Assessment Scale (CGAS) score of < 20

### Who will take informed consent? {26a}

Young people with psychiatric emergencies considered for inpatient admission within participating NHS CAMHS will be screened for trial suitability. The relevant clinical teams in each trust will explain the study to eligible participants and sufficient time will be given to read through the participant information sheet and ask questions, before deciding whether to take part. The trial research assistant from each centre will obtain consent and complete the baseline assessment prior to randomization.

